### Sample size

Patients with KOA will be randomized into two groups in a 1:1 ratio. The sample size for each group was calculated according to the following equation for a design with repeated measures [20] Additional file 2:$$ \mathrm{n}=\frac{2\kern0.5em *\kern0.5em {\upsigma}^2\kern0.5em {\left({\mathrm{u}}_{\alpha}\kern0.5em +\kern0.5em {\mathrm{u}}_{\upbeta}\right)}^2}{\updelta^2}\left\{\left[\frac{1}{\mathrm{r}}+\left(1-\frac{1}{\mathrm{r}}\right)\uprho \right]-\frac{\uprho^2}{1/ P+\left(1-1/ P\right)\rho}\right\} $$

where *P* stands for the number of observations prior to acupuncture (VAS score before the first intervention, one time point before treatment), and *r* is the observation number after acupuncture (VAS scores at the end of the 1^st^, 3^rd^, 6^th^, 9^th^, and 12^th^ treatments, a total of five time points after treatment). The values of ρ, α, μ_α_, and μ_β_ used here are as follows: ρ = 0.70 (usually between 0.50 and 0.75); α = 0.05 (bilateral); μ_α_ = 1.96; μ_β_ = 0.8417. As a result, an estimated sample size of 37 patients per group was obtained, assuming that a minimal difference of δ = 10 mm is considered as a clinically significant relief of chronic pain, as recommended by IMMPACT [21], and with a standard deviation (σ) of 29.5 mm of the VAS score for knee pain in all patients prior to treatment, according to the data from the clinical trial run by White et al. [22]. Considering a possible loss to follow-up of 20% Additional file 2, we planned to include total of 88 patients in our study.

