#### Knee pain intensity

To evaluate the efficacy of acupuncture treatment for KOA, knee pain intensity is measured via a 0–100 mm visual analog scale (VAS). The patient moves the slider on a 100-mm VAS ruler to indicate the intensity of knee pain that he/she is suffering, where the left end of the ruler marks “no pain,” and the right end marks “intolerable pain.” The distance (in millimeters) from the slider to the left end of the ruler is read directly from the back of the ruler by the researcher and is used as the VAS score for pain intensity, which is the primary outcome index in this study. The VAS score for knee pain intensity will be measured before each treatment and at the end of the 1^st^, 3^rd^, 6^th^, 9^th^, and 12^th^ treatments, as well as at the end of the follow-up visit (Fig. 3). Additional file 2

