### Statistics

All data will be analyzed using SPSS for Windows 17.0 Software (SPSS Inc., Chicago, IL, USA). For the main analysis, we will perform both an intent-to-treat principle and a per-protocol analysis. Measurement data will be described with mean ± standard deviation ($$ \overline{x} $$ ± SD), and count data will be expressed with number of cases and percentages. All statistical analyses will use two-tailed tests, and the level of significance will be set at *p* < 0.05 Additional file 2. 

Demographic and baseline characteristics of study participants by randomization group will be analyzed by an independent sample *t* test, *t*' test, or nonparametric test. In the comparison between the *De Qi* and control groups, the primary outcome (VAS scores) and secondary outcome (KOOS, in the form of symptom scores) will adopt the method of within-subject 6 × 2 factorial repeated measures analysis of variance (ANOVA) to analyze the integral analgesic effect, where the factors are time (six levels: baseline, and at the end of the 1^st^, 3^rd^, 6^th^, 9^th^, and 12^th^ treatments) and group (two levels: *De Qi* group and the control group). The immediate analgesic effect will be evaluated by the VAS score after the first treatment; the accumulated analgesic effect will be rated by the VAS score after the last treatment. They will be analyzed by the independent sample *t* test and *t*' test or nonparametric test. In addition, the overall *De Qi* scores of each group, i.e., the sum of the scores of all sensations in each treatment, will be considered and analyzed with the primary outcome by a bivariate correlation test (described by *r* and *p*).

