The aim of this study is to explore the analgesic effect (including immediate and accumulated analgesic effects) of *De Qi* induced by acupuncture in KOA patients. Different needling depths with or without needle manipulation will be used to induce or avoid *De Qi*. The actual *De Qi* sensations will be assessed with a *De Qi* scale (C-MMASS). The correlation between the overall *De Qi* scores and VAS of knee pain will also be analyzed to reveal the contribution of *De Qi* to the therapeutic effects. This trial will help to provide a clinical basis for further investigation of the relationship between *De Qi* and the therapeutic efficacy of acupuncture.

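### The immediate and accumulated effects are tested on post-treatment VAS without baseline adjustment, which gives about 31–36% power for 10 mm and lets chance baseline imbalance into the estimate

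*Protocol article*

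**What the plan says.** The Discussion sets out the purpose: "The aim of this study is to explore the analgesic effect (including immediate and accumulated analgesic effects", and the Abstract names the same two effects. The Statistics section then fixes how each is assessed. For the first, "The immediate analgesic effect will be evaluated by the VAS score after the first treatment"; for the second, "the accumulated analgesic effect will be rated by the VAS score after the last treatment". On the method it says "They will be analyzed by the independent sample" t test, the t' test or a nonparametric test. No change score and no covariate is named.

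The pre-treatment score is available. Under Knee pain intensity, VAS "will be measured before each treatment and at the end of the" 1st, 3rd, 6th, 9th and 12th treatments. The Abstract links the before-and-after pair at the first session to the immediate effect.

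Baseline does enter the 6 × 2 repeated measures ANOVA, as one of six time levels, but the Statistics section assigns that analysis to the integral analgesic effect.

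The Sample size section uses a repeated-measures formula with one pre-treatment and five post-treatment observations and a correlation of 0.70. Its target is that "a minimal difference of δ = 10 mm is considered as a clinically significant relief of chronic pain".

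**The concern.** An analgesic effect of a session or a course is relief relative to where the patient started. Comparing only the end score leaves the differences between patients that were present before needling in the error term. With a correlation of 0.70, the baseline score explains 0.70² = 0.49 of the variance of a later score, so about half of the noise in each test could be removed with data already collected.

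Two consequences follow, and they are two views of the same lost precision. A real 10 mm effect would be missed about two times in three. And in an 88-patient trial, whatever baseline difference arises by chance is carried in part into the observed estimate. The Background calls the role of De Qi controversial, so a non-significant result from such a test could be misread as evidence that De Qi does not matter.

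**Working it through.** **Inputs, all from Sample size:** σ = 29.5 mm (pre-treatment SD), δ = 10 mm, ρ = 0.70, "α = 0.05 (bilateral") so u_α = 1.96, "μ_β_ = 0.8417" (80% power), P = 1, r = 5, 37 per group, 88 in total (44 per group).

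**The plan's own figure.** The bracketed factor is [1/5 + (4/5)(0.70)] − 0.70² = 0.76 − 0.49 = 0.27. Then

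n = 2 × 29.5² × (1.96 + 0.8417)² / 10² × 0.27 = 136.6 × 0.27 = 36.9, so 37 per group. The stated figure is reproduced. The −0.49 term is the credit for adjusting for one baseline score.

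**The tests actually planned.** For a single post-treatment score, replace 0.27 by the variance factor f of the method:

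- unadjusted post score: f = 1
- change from baseline: f = 2(1 − 0.70) = 0.60
- ANCOVA on baseline: f = 1 − 0.70² = 0.51

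Power = Φ(δ / (σ√(2f/n)) − 1.96), and n for 80% power = 136.6 × f.

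| Analysis | f | Power, 37/group | Power, 44/group | n/group for 80% |
|---|---|---|---|---|
| Mean of five scores, baseline-adjusted (sample size basis) | 0.27 | 80.1% | 86.4% | 37 |
| One score, ANCOVA | 0.51 | 53.3% | 60.5% | 70 |
| One score, change | 0.60 | 46.9% | 53.7% | 82 |
| One score, unadjusted (as planned) | 1 | 30.8% | 35.6% | 137 |

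For the planned test at 37 per group: 29.5√(2/37) = 6.86 mm; 10/6.86 − 1.96 = −0.50; Φ(−0.50) ≈ 0.31. The noncentral t gives 30.1% and 34.9% at 37 and 44 per group. If 20% of 44 are lost (about 35 per group), power is about 29%.

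**Detectable difference at 80% power, 37 per group.** Unadjusted: 2.8017 × 6.86 = 19.2 mm. ANCOVA: 19.2 × √0.51 = 13.7 mm.

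**Sensitivity to ρ.** Over the range the protocol calls usual (0.50 to 0.75), ANCOVA power is 39–60% at 37 per group and 45–67% at 44 per group, always above the unadjusted test. Before and after a single session the correlation may be higher. If it were 0.9 (an assumption, not in the protocol), then f = 0.19 and ANCOVA power for the immediate effect at 44 per group would be about 95%.

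**Baseline imbalance.** The standard error of the chance baseline difference is 29.5√(2/44) = 6.3 mm. Per standard error, 0.70 × 6.3 = 4.4 mm passes into the unadjusted comparison. At 37 per group the figures are 6.9 and 4.8 mm.

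**The case against.** **The wording may allow a change score.** The article is condensed, and the Abstract mentions measurements before and after the first session. But the Statistics section names the score after treatment for both effects and nothing else. Even on the change-score reading, power is 47–54%, still below ANCOVA.

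**The repeated measures ANOVA already uses baseline.** It does, and its group-by-time term compares change between arms. The protocol nevertheless gives it a different target and sends the two effects named in the aim to the t tests.

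**The shortfall from 80% is not all due to missing adjustment.** This is right. At 37 per group, going from the mean of five scores to one score costs about 27 points (80.1% to 53.3%), and dropping baseline costs about 22 more (to 30.8%). The split depends on the order: dropping baseline first takes 80.1% to 38.7%, and using one score then takes it to 30.8%. In either order, adjustment is a large part of the loss, but adjustment alone does not restore 80%.

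**The unadjusted test is valid.** Also right. Under randomisation it is unbiased and keeps its type I error. The imbalance figure is already contained in its standard error and is not a harm additional to the lost precision.

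**The SD comes from pre-treatment scores in another trial.** True, but the protocol's own formula makes the same equal-variance assumption.

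**Conclusion.** The concern holds. Both effects in the stated aim rest on comparisons that omit a baseline score the trial collects and its sample size calculation counts on. For a 10 mm difference the planned tests have about 31% power at 37 per group and 36% at 44 per group, less than half the 80% planned. ANCOVA gives 53% and 60%. The damage is loss of precision and an observed estimate that follows chance imbalance, not systematic bias.

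The figures assume that the 29.5 mm SD also applies after treatment and that the correlation is 0.70. The ranking of ANCOVA above the unadjusted test holds over the protocol's whole range of correlations; the size of the gain does not, and at ρ = 0.50 it is only about 8 to 10 points.

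**What to change.** Replace the two t tests by ANCOVA, or by the corresponding session contrasts from one baseline-adjusted repeated measures model. The outcomes are VAS after the first treatment and VAS after the twelfth, each adjusted for the VAS taken before the first treatment. Report the adjusted mean difference with its 95% confidence interval for each.

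State alongside that these single-visit contrasts have about 50–60% power for 10 mm at ρ = 0.70, and that the 80% in the sample size section belongs to the baseline-adjusted mean of five post-treatment scores. A non-significant contrast should then be read from its interval.

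The cost is analysis wording only, as the covariate is already collected. Trial status reports that recruitment is complete with treatment and follow-up still running, so sample size is no longer an open choice but the analysis is. Since groups stay coded until analysis is finished, the change can be recorded as pre-specified if it is dated before unblinding.

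### The immediate effect is tested on one unadjusted VAS score after session 1, although a pre-session-1 score and four further before/after pairs are collected and could sharpen or support it

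*Protocol article*

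**What the plan says.** The Statistics section defines the immediate effect thus: "The immediate analgesic effect will be evaluated by the VAS score after the first treatment". The test is an independent-sample t test, its unequal-variance form, or a nonparametric test. No change score and no baseline covariate is mentioned. The accumulated effect is handled the same way on the score after the last session. Separately, a 6 × 2 repeated measures ANOVA uses baseline and the five post-session scores.

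On data collection, the Knee pain intensity section states: "The VAS score for knee pain intensity will be measured before each treatment and at the end of the 1^st^, 3^rd^, 6^th^, 9^th^, and 12^th^" sessions, and again at the end of follow-up. Each patient therefore has five before/after pairs. The Abstract also describes measurement before and after these sessions. It assigns the first session to the immediate effect and the later ones to the accumulated effect.

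**The concern.** The immediate effect is one of two stated aims, but its test is the least precise analysis of that question that the collected data allow. The sample size was derived for a different analysis: five post-treatment scores averaged and adjusted for baseline. The immediate-effect test uses one score with no adjustment, so the planned size gives it little power. If the observed difference were zero, its confidence interval would still include the 10 mm that the protocol treats as clinically relevant.

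In addition, no described analysis uses the pre-session readings at sessions 3, 6, 9 and 12. The plan therefore cannot show whether what a single session does to pain persists or fades over the course.

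**Working it through.** **Inputs (Sample size section).** "α = 0.05 (bilateral"), so u = 1.96; "μ_β_ = 0.8417", that is 80% power; "minimal difference of δ = 10 mm is considered as a clinically significant relief of chronic pain"; "standard deviation (σ) of 29.5 mm of the VAS score for knee pain in all patients prior to treatment"; "ρ = 0.70 (usually between 0.50 and 0.75"); one observation before treatment ("VAS score before the first intervention, one time point before treatment") and r = 5 after it.

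**The plan's own figure.** The bracket in the formula is [1/5 + (4/5)(0.70)] − 0.70² = 0.76 − 0.49 = 0.27. Then n = 2 × 29.5² × (1.96 + 0.8417)² / 10² × 0.27 = 136.6 × 0.27 = 36.89, rounded up to 37. The stated 37 per group reproduces.

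**The same formula for the immediate-effect test.** One unadjusted score has factor 1.0, so n = 136.6, or 137 per group for 80% power. One score adjusted for one baseline has factor 1 − 0.70² = 0.51, so n = 136.6 × 0.51 = 69.7, or 70 per group.

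**Precision at 44 per group (88 in total).** SE = 29.5 × √(2f/44), where f is the variance as a multiple of σ². Half-width = 1.96 × SE. Power for 10 mm ≈ Φ(10/SE − 1.96).

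For the mean of five changes, each change has variance 2(1 − 0.70)σ² = 0.6σ². If changes at different sessions have correlation c, the mean has f = 0.6(1 + 4c)/5. A single common ρ between all readings implies c = 0, because the covariance of two changes is then ρ − ρ − ρ + ρ = 0. If some patients respond consistently better than others, c is above 0. The document gives no value for c, so the values below are assumptions.

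| Analysis | f | SE (mm) | 95% half-width (mm) | Power for 10 mm |
|---|---|---|---|---|
| Session 1, post score only (as planned) | 1.00 | 6.29 | 12.3 | 36% |
| Session 1, change score | 0.60 | 4.87 | 9.5 | 54% |
| Session 1, adjusted for baseline | 0.51 | 4.49 | 8.8 | 60% |
| Mean of five changes, c = 0 | 0.12 | 2.18 | 4.3 | >99% |
| Mean of five changes, c = 0.3 | 0.264 | 3.23 | 6.3 | 87% |
| Mean of five changes, c = 0.5 | 0.36 | 3.77 | 7.4 | 75% |
| Mean of five changes, c = 0.8 | 0.504 | 4.47 | 8.8 | 61% |

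At 37 per group, the size before allowance for loss, the planned test has SE 6.86 mm and 31% power; the adjusted one has 4.90 mm and 53%.

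**Sensitivity to ρ.** Over the protocol's range of 0.50 to 0.75, the adjusted session-1 SE at 44 per group is 6.29 × √0.75 = 5.45 mm down to 6.29 × √0.4375 = 4.16 mm. Adjustment beats the planned test throughout.

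**Pooling when the effect fades.** If the per-session effect fell from 10 to 2 mm in steps of 2 (assumed figures), the pooled mean would be (10 + 8 + 6 + 4 + 2)/5 = 6 mm, below the first-session effect of 10 mm.

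**The case against.** The strongest objection is that the protocol asks about session 1. The Abstract and the Statistics section agree on that, and only at session 1 is the before score a true pre-treatment baseline. Later before scores come after randomisation and may already carry accumulated effect. An arm that has improved more also has less room to fall. The pooled change is thus a different estimand. This stands, and it is why pooling can only be supportive.

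A reader might also infer three stronger things that the documents do not support:

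- *Most of the data are wasted.* Of the ten readings in the five pairs, six (baseline and the five post-session scores) enter the ANOVA, and the session-12 score is also the accumulated-effect endpoint. Only the four later pre-session readings, and the within-session changes, go unanalysed.
- *Pooling secures over 99% power.* That needs c = 0 and a similar effect at every session. At c = 0.8 the pooled SE is about the same as that of adjusted session 1.
- *One session cannot tell 0 from 10 mm.* This is true of the unadjusted test. The adjusted half-width of 8.8 mm is below 10 mm. Readings taken within one session may also correlate above 0.70: at an assumed 0.9 the adjusted SE is 29.5 × √(2 × 0.19/44) = 2.74 mm.

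Finally, supplementary models are often left to an analysis plan, which is not shown here. That excuses the absence of a longitudinal model. It does not cover the main point, because the article itself fixes the variable and the test for the immediate effect.

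**Conclusion.** The point holds in a limited form. Defining the immediate effect by session 1 is legitimate; testing it on the post-session score alone is needlessly imprecise. Baseline adjustment cuts the variance from 1.0 to 0.51σ², the SE from 6.3 to 4.5 mm, and raises power for 10 mm from about 36% to about 60% at 44 per group. These figures assume complete data, the protocol's SD applying after treatment as well as before, and ρ = 0.70.

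Even adjusted, the comparison stays below 80% power at that ρ, so a non-significant result should be read from its confidence interval. The later pairs can add information on persistence, and possibly precision. The size of that gain is unknown, because it depends on c and on how stable the effect is across sessions.

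**What to change.** In the Statistics section:

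1. Keep session 1 as the definition of the immediate effect, but compare the arms on post-session-1 VAS with pre-session-1 VAS as covariate, and report the adjusted difference with its 95% CI.
2. Add, labelled as supportive, one longitudinal model of within-session change (after minus before) at sessions 1, 3, 6, 9 and 12 with an arm × session term. Report session-specific and pooled differences with 95% CIs. State that the pooled figure is not the first-session effect, that its before scores after session 1 are post-randomisation, and that it can understate a first-session effect that fades.

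The cost is one covariate and one extra model, with no new measurements. The article reports treatment and follow-up still under way and has the statistician work with coded groups, so both changes could be specified before the groups are unmasked.

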#### Assessment of De Qi sensation induced by acupuncture

In our study, the assessment of *De Qi* sensation perceived by the patients is based on the Chinese version of the ”modified” Massachusetts General Hospital Acupuncture Sensation Scale (C-MMASS) (see Additional file 1). Before the trial, the concept of “*De Qi* and its correlated sensations” will be explained to all participants by the recorder. At the end of each treatment session after the removal of the needles, patients will be asked to fill in the C-MMASS form to evaluate the intensities of 11 acupuncture sensations: soreness, aching, deep pressure, heaviness, fullness/distension, tingling, numbness, dull pain, warmth, cold, and throbbing. The intensities of these sensations are evaluated on a 0–10 cm VAS, where 0 represents “none” and 10 represents “intolerably strong sense.” There is also an additional blank row at the end of the form that the patient can use to assess any other sensations. The MASS index will then be calculated.

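### The De Qi correlation uses raw VAS with no baseline adjustment, so it is a weak and possibly biased basis for stating De Qi's contribution

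*Protocol article*

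**What the plan says.** The Statistics section plans the randomised comparisons first (repeated measures ANOVA, then t tests after the first and last treatments). It then adds a further analysis and defines the score it uses: "the overall *De Qi* scores of each group, i.e., the sum of the scores of all sensations in each treatment". The method planned for this score is that it "will be considered and analyzed with the primary outcome by a bivariate correlation test", with r and p reported. The primary outcome is the VAS score for knee pain. Neither change from baseline nor any covariate is mentioned for this analysis.

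The Discussion states its purpose: the correlation "will also be analyzed to reveal the contribution of *De Qi* to the therapeutic effects".

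The arms differ in more than De Qi. Under Interventions, one arm is needled to 25–30 mm with manipulation and the other to 1–2 mm without. The Discussion says "Different needling depths with or without needle manipulation will be used to induce or avoid" De Qi. No planned analysis other than the correlation uses the De Qi score.

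Under Outcomes, the sensation scale is completed after every session (three a week for four weeks, so 12), while VAS is read at the end of only five of them (1, 3, 6, 9 and 12).

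**The concern.** The randomised contrast compares two needling techniques. Any statement about De Qi as distinct from depth and manipulation therefore has to lean on the correlation. Method, outcome and purpose are all stated, so this is not merely a detail left to a later document.

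Two weaknesses hold on every reading. First, raw VAS after treatment is strongly determined by pain before treatment, which adds noise unrelated to De Qi. Second, both quantities are patient ratings on visual analog scales, and the sensation scale includes soreness, aching and dull pain, rated after needling around a painful knee. If patients with more pain also report stronger sensations, De Qi and raw VAS correlate positively without any effect of De Qi. Since analgesia would show as a negative correlation, the same bias can hide a real effect.

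A third weakness is conditional: the text does not settle whether arms or sessions are combined, or which VAS is paired with which De Qi score.

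**Working it through.** **Inputs from the protocol (Sample size, Statistics):** σ = 29.5 mm, δ = 10 mm, ρ = 0.70, five post-treatment readings, one baseline reading, 88 patients at 1:1 (44 per arm), two-sided 0.05.

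**Assumed, because the protocol gives no De Qi distribution:** De Qi within-arm SD of 1 and within-patient correlation 0.70; arms 1 to 3 SD apart on De Qi; stated links between De Qi ratings and pain level.

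**1. The protocol's own figure.** There is none for the correlation. The sample size, from which ρ and σ are taken, reproduces: n = 2 × 29.5² × (1.96 + 0.8417)² / 10² × {[0.2 + 0.8 × 0.70] − 0.70²} = 136.62 × 0.27 = 36.89, so 37 per group.

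**2. Attenuation.** Given baseline, the variance of post-treatment VAS is (1 − 0.70²)σ² = 0.51σ². If De Qi is unrelated to baseline, r with raw VAS is √0.51 = 0.71 of r with baseline-adjusted VAS. Change has variance 2(1 − 0.70)σ² = 0.60σ², so against change the factor is √0.60 = 0.77. A baseline-adjusted r of −0.40 would appear as −0.40 × 0.71 = −0.28.

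**3. Spurious association, one arm, one session, De Qi inert.**
- If De Qi correlates 0.3 with baseline VAS and is linked to later VAS only through it, r with raw VAS = 0.70 × 0.3 = +0.21.
- If De Qi reporting instead correlates b with a stable underlying pain level, r = √0.70 × b × √0.70 = 0.70b, that is 0.14 for b = 0.2 and 0.28 for b = 0.4. By Fisher z with n = 44, atanh(0.14) × √41 = 0.90 and atanh(0.28) × √41 = 1.84, so p < 0.05 in about 15% and 45% of trials. Simulation (1,500 runs) gave 14% and 47%. With no link it gave 4% to 6%.

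**4. Does using baseline cure it?** In the stable-level cases, change from baseline within the arm gave about 5% and 6%. A partial correlation given arm and baseline VAS (all 88 patients) still gave 9% and 21%, because one baseline reading measures the underlying level with error. The order can reverse. In the first case of step 3, baseline adjustment removes the bias, while change has covariance 0.21 − 0.30 = −0.09 and r = −0.09/√0.60 = −0.12. Neither is safe under every mechanism, so both should be shown.

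**5. Only if arms or sessions are pooled, De Qi inert.**
- Arms pooled, one session: r = −(D/2)(d/2)/√[(1 + D²/4)(1 + d²/4)], with D the arm difference in De Qi (SD units) and d the arm difference in VAS divided by 29.5. D = 2 and 10 mm gives r = −0.12, significant in about 20% of trials at n = 88. D = 3 and 15 mm gives r = −0.21 and about 48%. Simulation at 10 mm, over D = 1 to 3, gave 12% to 25%.
- Five sessions pooled as independent pairs: 26% to 30% with no arm effect; 45% to 71% with a 10 mm arm effect and arms also pooled.
- The biases can offset. With arms pooled, 10 mm and D = 2, mean r moved from −0.12 with no pain link to −0.03 at b = 0.2 and +0.08 at b = 0.4.

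**The case against.** A reader might infer that the protocol specifies pooling of arms and sessions. It does not. The words "of each group" can naturally mean one correlation per arm, which removes the confounding by arm. The words "in each treatment" can mean one per session, which removes the repeated pairs, though it gives up to 2 × 5 = 10 tests. The figures in step 5 are therefore conditional, and much of this detail is what an article may leave to a fuller document.

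A reader might also infer that two De Qi scores compete, because the assessment section says "The MASS index will then be calculated" while the Statistics section uses a sum. But the Statistics section names the score it analyses, and the index formula is not in the document, so how far the two differ cannot be judged. At most this needs a clarifying sentence.

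It is also fair that the correlation is supplementary, that the aim is worded as exploratory, that the protocol never says the correlation is meant to separate De Qi from depth and manipulation, and that step 3 rests on an assumed link between sensation ratings and pain. With no link, a within-arm, single-session test keeps its nominal level.

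What remains is that raw VAS is used with no baseline, the loss of sensitivity follows from the protocol's own ρ, and the purpose given in the Discussion is stronger than an unadjusted, non-randomised association can support.

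**Conclusion.** The point holds in this limited form. On any reading, correlating De Qi with raw VAS shrinks a true association to about 0.71 of its baseline-adjusted size (0.77 against change), given ρ = 0.70 and De Qi unrelated to baseline. If De Qi ratings track pain level, the correlation is also biased upwards, with 14% to 47% false positives under assumed links of 0.2 to 0.4. Confounding by arm and inflation from repeated pairs are ambiguities to be closed, not errors that the protocol commits.

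No version of this analysis can establish De Qi's causal contribution, because De Qi intensity within an arm is not randomised. The randomised comparison of the two techniques is unaffected.

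**What to change.** - Relate the De Qi score to change in VAS from the reading before the first treatment, with baseline-adjusted VAS as a sensitivity analysis. If the two disagree, say so.
- State that the analysis is within arm or adjusted for arm.
- Pair each session's De Qi score with that session's post-treatment VAS (sessions 1, 3, 6, 9 and 12).
- If sessions are combined, use a mixed model with a patient random effect that separates within-patient from between-patient De Qi.
- Report the slope with its 95% CI as an exploratory, non-randomised association, and replace the Discussion's wording about revealing De Qi's contribution.
- Word the randomised conclusion as deep, manipulated needling against superficial, unmanipulated needling.

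The cost is a more cautious statement about De Qi and slightly more analysis work. No new data are needed: baseline VAS and session scores are already in the schedule, and Trial status shows treatment and follow-up still under way, so the wording can be settled before the analysis.
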